### Sample size

The sample size calculation was based on the primary endpoint, the BI, for which we model the cumulative probability that the i-th BI Y_it_ will fall into the j-th category or below:

1$$logit\left(P\left({Y}_{it}\le j\right)\right)={\theta}_j-{\delta}_1\left(t{1}_{it}\right)-{\delta}_2\left(t{2}_{it}\right)-u\left({patient}_i\right)$$

i corresponds to the index for observations at time t, j represents the index for categories, {*θ*} is the cut-points, *δ*1 corresponds to the change in BI between PAC entry (baseline) and PAC exit, and δ2 is the change in BI between PAC entry and follow-up measurement at home after 6 months. Patient effects (random effects) are designed as independent and identically normally distributed:

2$$u\left({patient}_i\right)\sim N\left(0,{\sigma}_u^2\right)$$

Of vital importance for the evaluation of the sustainability of PAC is parameter δ2, for which the following hypothesis will be tested:

3$${H}_0:{\delta}_2\le \kern0.5em 0.4,\kern1.5em {H}_1:{\delta}_2>0.4$$

The expected improvement in BI under the alternative hypothesis is >0.4 logits, which corresponds to an odds ratio (OR) of about 1.5. The required sample size to detect an effect under the alternative hypothesis was determined by simulation. We assumed a significance level of α = 0.05 (two-sided test) and a target power of 0.8 (β = 0.2). The obtained power is based on 500 iterative analogue model estimates and was performed for different levels of patient-specific autocorrelation (intra-class correlation [ICC] = 0.1, 0.2, 0.4). As is usual with mixed-effects models, the sample size decreases with increasing ICC (see Fig. 1).

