Treatments with a rehabilitative approach are characterised by close interprofessional cooperation focusing on functional activities, education and psycho-social support [37]. Physicians are primarily responsible for PAC assessment, drug treatment, follow-up and evaluation. Therapeutic specialists, such as physiotherapists and occupational and speech therapists, are tasked with improving functioning, and nurses transfer and integrate (re)gained functions into the daily lives of older people. For example, the handgrip strength regained through targeted physiotherapy is transferred to everyday life through targeted nursing interventions. Patients are given sufficient time and individual support to select, prepare and eat their bread rolls for breakfast independently instead of simply feeding them. Overall, providing advice, particularly on mobility and self-care, to patients and their caregivers is an essential nursing intervention in PAC [37]. Social service providers carefully plan the return home and subsequent outpatient care. Furthermore, they initiate necessary measures in collaboration with the primary relatives.

A PAC programme lasts an average of 8 weeks and a maximum of 10 weeks based on the PAC potential assessment. If, after this time span, a return home is not possible, even with appropriate support, suitable alternatives are explored together with the affected person. In cases where a return home is likely after an extended stay, the older person is transferred to a specialised nursing ward to attain adequate independence and functioning.

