### Endpoints

The following outcomes will guide the evaluation of the PAC programme.Functional status as the primary endpoint

Functional status will be measured with the BI [38] at PAC entry (T0), PAC exit (T1) and 6 months after PAC discharge to the home environment (T3). The BI is a ten-item scale with either 0, 5, 10 or 15 points allocated for each item (maximum total score of 100 points = maximum functional status). The BI is a validated and common instrument used to assess functionality in rehabilitation care [38, 39]. For use with older and multi-diagnosed people, there might be imprecision when testing takes place by different observers [40]. To the best of our knowledge, little is known about the sensitivity to changes in the BI [41]. A clinically meaningful change is to be determined by the patients themselves. Recommended BI cut-off points to determine overall independence are problematic. Overall, a five-point difference can have completely different meanings for individual daily life independence. Collin and colleagues [39, 41] recommended that a 20-point change be considered as clinically significant. For the individual use of BI, other endpoints must also be considered.

All items will be collected through direct observation by study personnel or interviews with those affected, their relatives or the nursing staff.2.Independence as the secondary endpoint

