
Data from the study participants will be routinely collected four times (see Table 1). Socio-demographic data of the participants will also be collected, particularly to analyse sex-specific aspects.

**Table 1 Tab1:** Outcome Measurements during the Intervention Schedule

Timepoint	T0	T1	T2	T3
	PAC admission	PAC discharge	3 months after discharge	6 months after discharge

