**Secondary Outcomes**				
**· Delirium (DOS)**	+			
**· Cognition (MMSE)**	+			+
**· Mobility (SPPB)**	+			+
**· Falling concerns (FES-I)**	+			+
**· Frailty**	+			+
**· Weight, height, BMI**	+			+
**· PAC capability**	+	+		
**· Quality of life**	+	+		+
**· Informal network**				+

Ninety days after PAC discharge, telephone contact will be established with the older person to ask whether they want to continue participating in the study and to verify their address.

As part of the process evaluation, the primary relatives (*n* = 30) will be individually interviewed 6 months after PAC discharge using constructive grounded theory to identify impacts of the PAC programme on their quality of life during their daily routines [56]. These interviews will be conducted by trained PZZ staff members not involved in the PAC programme.

The timepoints are labelled T0 to T3. The plus symbol (“+”) indicates the timepoints at which each instrument will be applied. At T2, no outcomes will be evaluated, but the participants’ residence and continued participation will be verified.

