If the results of this study show that PAC programmes delivered in nursing homes improve the participants’ functional status to the point that they can return home, then the tested programmes could be considered an effective way to delay the elderly from permanently residing in a nursing home. Furthermore, having evidence of a successful PAC programme will offer specialised nursing homes the opportunity to differentiate their services and transform their image from the “last station in life”. Having access to a comprehensive geriatric assessment tool will also enable PAC staff to develop treatment plans, which decreases the probability that older people will be institutionalised [7, 9].

According to the British Medical Research Framework for complex interventions [61], this study is categorised as a pilot study to determine whether the PAC programme can improve older people’s functional status, as measured using the BI. Moreover, the repeated measures study design allows the assessment of functionality over several months and ensures that the intervention’s short-term and long-term effects can be adequately captured and differentiated [62].

In sum, we will determine the sustainability of the PAC programme from the perspectives of the elderly and their relatives over 6 months. We expect that the PAC programme will improve the functional status of older people and reduce the burden on their relatives.

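### The 6-month Barthel Index has no defined time point for patients who do not return home, which can bias δ2 upward, and return home itself is not an endpoint

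*Protocol article*

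**What the plan says.** **Primary time point.** The Sample size section singles out δ2 as the key parameter for sustainability and defines it as "the change in BI between PAC entry and follow-up measurement at home after 6 months". The Endpoints section measures the BI at PAC entry, "PAC exit (T1) and 6 months after PAC discharge to the home environment (T3"). The MMSE entry also puts T3 at home. Table 1 is neutral: its T3 column reads only "6 months after discharge".

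**Patients who do not go home.** PAC lasts at most 10 weeks. The Intervention section then says: "If, after this time span, a return home is not possible, even with appropriate support, suitable alternatives are explored together with the affected person". It also describes transfer to a specialised nursing ward when a return home is likely only after a longer stay. Neither group is given a T3.

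**Residence.** The aims and hypothesis include reaching a level of function that allows return home. The Discussion draws its conclusion from whether PAC improves "functional status to the point that they can return home, then the tested programmes could be considered an effective way to delay" permanent nursing-home residence. At T2 the participants' "residence and continued participation will be verified", but the same note says that no outcome is evaluated then. The endpoint list and Table 1 contain no discharge destination, residence or vital status.

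**The concern.** Whether a T3 value exists depends, for some patients, on where they live 6 months on. The Background links reduced functional and cognitive status to the need for long-term care, so by the protocol's own reasoning, residence at 6 months is related to the outcome being measured.

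If the missing T3 values belong mainly to patients who declined after PAC, δ2 will look better than it is in the patients who entered PAC. The study has no control group, so no comparison arm would reveal this. The planned statement about returning home would also rest on BI scores alone, without a count of who was living at home.

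**Working it through.** **1. The plan's own figures.** exp(0.4) = 1.49, which agrees with the stated odds ratio of about 1.5. 200 × (1 + 0.30) = 260, the stated enrolment. With 30% lost, 260 × 0.70 = 182 remain, and 200 / 0.70 = 285.7, so 286 would be needed to keep 200. That shortfall is a separate point. Here it matters only that inflating the number replaces patients and does not correct selection.

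**2. Who has a T3, by the wording.**
- At home at 6 months: defined in every section.
- Discharged home, later institutionalised: the Endpoints wording can be read as fixing only the starting date, and Table 1 names no setting. The Sample size section and the MMSE entry say at home. The text conflicts.
- Never discharged home, including ward transfers who stay: the T3 clock has no starting date.

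**3. Size of a possible bias.** Two separate simulations of equation 1 were run with 260 enrolled. The cut-points and the true δ1 are not published, so they are assumed, as is the strength of the missingness.
- Simulation A: ICC 0.2 and 0.4, 10 categories, δ1 = 0.4, 200 runs per setting, T3 lost with a logistic probability in standardised T3 latent function.
- Simulation B: ICC 0.2, 8 categories, δ1 = 0.6, 80 runs per setting. Monte Carlo error of the mean is about 0.17/√80 = 0.02.

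All patients keep T0 and T1. Bias = mean estimate − true δ2.

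| T3 loss | Share lost | Mean estimate, true δ2 = 0 | Mean estimate, true δ2 = 0.4 |
|---|---|---|---|
| A: unrelated to function | 30% | 0.015 | about 0.42 |
| A: odds of loss double per SD lower T3 function | 30% | 0.343–0.355 | about 0.76 |
| A: odds of loss triple per SD lower T3 function | 30% | 0.484–0.499 | 0.90–0.91 |
| B: random | 30% | 0.007 | 0.410 |
| B: lowest T1 function | 30% | 0.009 | 0.409 |
| B: partly on T3 function | 10% | 0.164 | 0.569 |
| B: partly on T3 function | 30% | 0.469 | 0.879 |
| B: lowest T3 function always lost | 10% | 0.317 | 0.752 |
| B: lowest T3 function always lost | 30% | 0.926 | 1.355 |

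Loss that depends only on T1 function gives a bias of 0.01. Partial dependence on T3 function gives 0.16–0.17 at 10% loss (26 of 260 patients) and 0.47–0.48 at 30% (78 of 260). Simulation A gives about 0.34–0.36 (doubling) and 0.48–0.51 (tripling). The last two rows are an extreme bound and not an expectation.

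**4. Consequence for the test.** With true δ2 = 0, Simulation A rejects δ2 = 0 in 46–53% of runs (doubling) and 80–84% (tripling). The printed null is δ2 ≤ 0.4. Against that null, Simulation B with 30% loss and partial dependence rejects in 6% of runs when true δ2 = 0 and in 82.5% when true δ2 = 0.4 (two-sided 5% criterion). At 10% loss these become 0% and 11%. With random loss and true δ2 = 0.4 the figure is 1%.

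**The case against.** **The wording may not exclude institutions.** The Endpoints section dates T3 but does not clearly say where the BI is taken, and it allows items to be obtained from nursing staff. This stands for patients who went home and were later institutionalised: for them the fault is a conflict in wording, not a clear exclusion. It does not help those who never went home.

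**Few patients may be affected.** The Abstract limits entry to people likely to go home within 8 weeks. This shrinks the group, although the inclusion list under Participants does not repeat the condition and the Intervention section still foresees non-return. Some of the 30% dropout will also be voluntary withdrawal, since continued participation is asked about at 90 days. The share lost for reasons of function is unknown.

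**The mixed model uses T0 and T1.** Correct. A reader might infer that δ2 is estimated only among patients who succeeded. It is not: patients without T3 stay in the model, and non-return already decided at PAC exit may be largely explained by the observed T1 score. The bias comes from decline, institutionalisation or death after T1.

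**The rejection rates.** A reader might take 46–84% as the trial's false-positive rate. Those figures test δ2 against zero, which is not the printed hypothesis. Against the printed null the rate is low when there is no true change, although it is inflated at the boundary of 0.4.

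**Missing-data methods belong in an analysis plan.** They may, and their absence here is no fault. The endpoint definition and the endpoint list are stated in this article, however, and no analysis plan can recover BI scores that were never collected.

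**It is an exploratory pilot.** This tempers how strongly the result will be read, but the article still plans a conclusion about return home.

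**Conclusion.** The point holds in this form. T3 is undefined for patients who do not return home and ambiguous for those institutionalised later. Upward bias in δ2 is conditional: about zero if loss depends only on function seen by T1, and positive if loss reflects decline after T1, which the Background makes plausible. Under the assumed dependence it is about 0.16 logits (10% loss, partial dependence) to 0.35–0.5 logits (30% loss, moderate to strong dependence), equivalent to odds ratios of about 1.17 to 1.65 with no true change, against a target of 0.4 logits. Neither the share lost for functional reasons nor the strength of the dependence can be taken from the document, so the direction is supported and the size is not known.

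Return home is part of the hypothesis and the planned conclusion but is not an endpoint. It would go too far to say that residence is never looked at: it is verified at T2, but not analysed.

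**What to change.** - Define T3 as 6 months after PAC exit for every enrolled patient, and obtain the BI wherever the patient then lives.
- Bring the Sample size section, the primary and secondary endpoint descriptions and Table 1 into line with that definition.
- Add residence and vital status (home, institution, dead) at T1 and T3, and at T2 where residence is already verified, as a secondary endpoint. Report the proportion of all enrolled patients living at home, with its 95% confidence interval.
- Optional, and suitable for the analysis plan: a sensitivity analysis of δ2 with death as the lowest ordinal category, which the cumulative-logit model accepts directly. Collecting the BI in institutions cannot remove loss through death.

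The cost is small: revised wording, some T3 assessments in institutions and one added status variable. Information from nursing staff is already an accepted source for the BI. The change has to be made before the T3 assessments concerned would fall due.

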Independence will be measured via the informal network and the following nine criteria: delirium, cognition, mobility, falling concerns, frailty, body mass index (BMI), PAC capability and quality of life. The details of each criterion are as follows:Delirium: The assessment of delirium will be performed with the Delirium Observational Scale (DOS) at PAC entry (T0) [42]. The instrument has shown a high internal consistency with a reported Cronbach’s alpha = 0.96 and is considered valid and reliable for the early detection of delirium in older people [37, 38]. Delirium per shift will be evaluated using 13 items and four levels (never, sometimes, always or do not know). The occurrence of more than three criteria indicates a positive delirium screening and will trigger additional assessment.Cognition: The degree of cognitive performance will be measured using the Mini-Mental State Examination (MMSE) at admission (T0) and at home (T3) [43]. The reliability of the MMSE has been reported with a reported Cronbach’s alpha = 0.91 [44]. The sum of the MMSE spans from zero to 30 points, with 30 being the optimal result. Cognitive impairment is diagnosed at an MMSE sum of less than 24 points [43, 45, 46].Mobility: Mobility will be measured using the Short Physical Performance Battery (SPPB) at PAC entry and 6 months after release from the PAC to the home environment (T0, T3) [47]. SPPB has proven reliable with a Cronbach’s alpha = 0.87 [48]. The SPPB includes balance, a four-metre walking test and the stand-up test. A score of 10–12 points represents normal mobility, a score of 7–9 points indicates an increased risk of gait disorder and a score of less than 6 points indicates a very high risk of increasing gait disorder and loss of independence [47].Falling concerns: Concerns regarding falls will be measured with the German version of the Falls Efficacy Scale-International (FES-I) at PAC entry and 6 months after release from the PAC to the home environment (T0, T3). The German version of the FES-I has a high internal consistency (Cronbach’s α = 0.96) and retest-reliability (*r* = 0.96) [49]. The FES-I questionnaire consists of 16 items in which concerns about different activities and cases are raised. The answers are graded as follows: one = no concerns; two = some concerns; three = moderate concerns; and four = very great concerns. A minimum score of 16 indicates no concerns about falling, and a maximum score of 64 indicates severe concern about falling [49, 50].Frailty: Frailty will be assessed using the frailty screening questionnaire [51, 52] at PAC entry and 6 months after release from PAC to the home environment (T0, T3). The questionnaire has been shown to be a valid and reliable instrument with a test-retest reliability total score of *r* = 0.937 [53]. The frailty screening questionnaire examines five factors (weight loss, fatigue, walking speed, physical weakness and activity level). The assessment is “met” or “not met”, with zero factors met indicating robustness, one to two factors met indicating a pre-frail status and less than three factors met indicating frailty [51, 52].Weight/height/BMI: Weight, height and BMI measures will be used as co-variates of frailty [8, 54]. All three elements will be measured at entry and 6 months after release from PAC to the home environment (T0, T3) [8].PAC capability: PAC capability assessment will be conducted using the Resident Assessment Instrument for Nursing Homes (RAI_NH) to determine the degree of care dependency at PAC entry (T0) and at PAC discharge (T1). The “Minimum Data Set” category of the Swiss RAI_NH is a needs assessment tool [55]. The RAI_NH care dependency score ranges from tier 1 (lowest) to 12 (highest) [55]. All items will be collected through direct observation or interviews with those affected, their relatives or the nursing staff.Quality of life: Quality of life will be measured as a subjective screening of health status on a numeric rating scale ranging from “excellent (10)” to “poor (0)” as an influence on functionality. It will be measured at entry, discharge and 6 months after release from the PAC to the home environment (T0, T1 and T3).Informal network: The frequency of use of formal and informal caregiver networks to secure the home environment will be measured by interviewing the primary relative in charge. The frequency of informal network use will be measured 6 months after discharge from PAC to the home environment (T3).

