### Statistical analysis

Data analysis will be performed using R-Project software version 3.5.2. The socio-demographic data will be analysed descriptively (frequencies, central tendencies, standard deviations). For the primary endpoint, the BI, we will estimate unadjusted cumulative odds using the basic model presented in the sample size section to detect BI changes between baseline and follow-up measures. The model will further be adjusted for age, sex, and secondary endpoints mobility and frailty, which have been identified as driving factors leading to institutionalisation in a nursing home. Both unadjusted and adjusted OR with corresponding 95% confidence intervals will be reported. Similarly, unadjusted and adjusted generalised linear mixed-effects models of the appropriate family and link function will be used to estimate the parameters of the secondary endpoints. Statistical significance will be established at *p* < 0.05.

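### The printed frailty classes overlap and omit 3 to 5 factors, and an SPPB score of 6 has no band, so neither secondary endpoint can be classified as written

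*Protocol article*

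**What the plan says.** Both rules are in the Endpoints section of the protocol article, under the secondary endpoint of independence.

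- **Frailty, items:** "The frailty screening questionnaire examines five factors (weight loss, fatigue, walking speed, physical weakness and activity level"). Each is recorded as met or not met.
- **Frailty, classes:** "with zero factors met indicating robustness", then "one to two factors met indicating a pre-frail status and less than three factors met indicating frailty".
- **Mobility (SPPB), upper bands:** "A score of 10–12 points represents normal mobility, a score of 7–9 points indicates an increased risk of gait disorder".
- **Mobility (SPPB), lowest band:** "a score of less than 6 points indicates a very high risk of increasing gait disorder and loss of independence".

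Table 1 schedules both instruments at T0 and T3 only. The Statistical analysis section uses the two variables again for the primary endpoint. It first states that "we will estimate unadjusted cumulative odds using the basic model presented in the sample size section", and then: "The model will further be adjusted for age, sex, and secondary endpoints mobility and frailty". Unadjusted and adjusted odds ratios are both to be reported with 95% confidence intervals. The article gives no other cut-off for either instrument.

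**The concern.** A classification rule has to place every possible score in one class and only one. The frailty rule fails on both counts, because its last class is defined by an upper limit where a lower limit is needed. The patients with the most factors met are the ones left without a class. The SPPB rule has no overlap but has a gap at one score.

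Frailty and mobility are secondary endpoints compared between T0 and T3. If the classes are analysed and the rule is programmed literally, counts of 3 to 5 become missing, and the class given to counts of 0 to 2 depends on the order of the code statements. A patient who improves from four factors to two would move from no class to two classes at once. The same variables are named as adjusters in the Barthel Index model, so there is a possible second route by which the error could reach a reported result.

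**Working it through.** The plan gives no figure to reproduce. The check is an enumeration of each possible score against the printed limits.

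**Inputs.** The five factors and the three frailty classes come from the Frailty item, and the three SPPB bands from the Mobility item. The SPPB maximum of 12 is in the text. The minimum of 0 is an assumption; it affects only the number of scores counted, not the gap at 6.

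**Frailty, as printed.** Robust: k = 0. Pre-frail: 1 ≤ k ≤ 2. Frail: k < 3.

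| Factors met (k) | Robust | Pre-frail | Frail | Number of classes |
|---|---|---|---|---|
| 0 | yes | – | yes | 2 |
| 1 | – | yes | yes | 2 |
| 2 | – | yes | yes | 2 |
| 3 | – | – | – | 0 |
| 4 | – | – | – | 0 |
| 5 | – | – | – | 0 |

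Three of six counts are classified twice, three of six are not classified, and 6 − 3 − 3 = 0 are classified once.

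**Frailty, with the last limit changed to k ≥ 3.** Count 0 is robust, 1 and 2 are pre-frail, and 3, 4 and 5 are frail. All six counts have exactly one class.

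**SPPB, as printed.**

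| Score | Band | Number of scores |
|---|---|---|
| 0–5 | very high risk | 6 |
| 6 | none | 1 |
| 7–9 | increased risk | 3 |
| 10–12 | normal | 3 |

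The total is 6 + 1 + 3 + 3 = 13 scores, of which one has no band and none has two. Extending either neighbouring band to include 6 would close the gap. The article does not show which one is meant.

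**Reach into the Barthel Index analysis.** The basic model in the Sample size section contains cut-points, two time effects (δ1 and δ2) and a patient random effect. It contains neither frailty nor mobility, and it is the model in which the hypothesis on δ2 is stated. Only the adjusted version includes the two variables. The Statistical analysis section does not say whether they enter as classes or as the factor count and SPPB total:

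- As raw scores, the cut-offs play no part, and the adjusted odds ratio is unchanged by the error.
- As the printed classes, coded literally, the error carries through. With complete-case fitting, patients with 3 to 5 factors would drop out.

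**The case against.** The best defence is that the frailty error is a slip whose meaning the sentence itself reveals. Zero and one to two are already assigned, so only 3 to 5 is left for the frail class, and the instrument's sources are cited. A careful analyst would probably notice. This stands as an account of what was intended. It does not make the printed rule usable: the limit is spelled out in words, so no inequality sign was lost in text extraction, and nothing else in the article corrects it. It also does not help with the SPPB, where the text gives no way to tell which band should hold a score of 6.

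It can also be said that the bands are there to interpret scores, and that how covariates are coded is commonly left to an analysis plan or full protocol. That is fair. The unstated coding is not itself a defect here, and it means that harm to the adjusted model cannot be asserted.

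Two stronger readings are tempting, and the article supports neither:

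- **That the error compromises the primary result.** The test of δ2 sits in the unadjusted model, which uses neither variable. The adjusted model is exposed only under categorical entry.
- **That the rule reverses frail and not frail.** As printed it gives two classes or none. A reversal needs a further step: applying only the last clause and treating everyone else as not frail.

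Finally, the counts above are counts of possible scores. The article gives no distribution of frailty or SPPB in this population, so the number of patients affected cannot be estimated.

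**Conclusion.** The defect is real and is wrong as written. It is an error in stating the cut-offs for two secondary endpoints. For frailty it is complete, since no count has a unique class; for the SPPB it concerns one score.

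The consequence is conditional. Categorical reporting of frailty or mobility from T0 to T3 is affected if the limits are coded as printed. The adjusted Barthel Index odds ratio is affected only if those classes are the covariates, and the unadjusted analysis of δ2 is not affected. Confidence is high for the wording error. No size can be put on any bias, because neither the covariate coding nor the score distribution is given. The correction is worth making because it is specific and nearly free.

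**What to change.** 1. **Frailty item:** define the frail class as three or more factors met, so that the classes are 0, 1–2 and 3–5. The other two classes already determine this, so no outside source is needed.
2. **Mobility item:** reconcile the SPPB bands with the cited scoring source so that a score of 6 falls in exactly one band. The choice should come from that source, since the article does not settle it.
3. **Optional:** add one sentence stating that the T0 factor count and T0 SPPB total are the covariates in the adjusted Barthel Index model. The model would then not depend on the bands. T0 values also precede the programme, and neither instrument is applied at T1, where the Barthel Index is measured. This is a modelling choice that the error does not force, and entering the scores as single numeric terms would assume linear effects on the logit scale.

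The cost is two corrected phrases in the protocol, the matching lines of analysis code and, if the third item is taken up, one sentence. No data collection or sample size changes.
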